### Inclusion criteria

Females aged 25–40 years.Meeting the WHO diagnostic criteria for infertility (failure to achieve clinical pregnancy after ≥12 months of regular unprotected intercourse).History of ≥2 unsuccessful IVF-ET cycles with availability of ≥1 good-quality cryopreserved embryo.Normal ovarian reserve ((AMH ≥1.1 ng/mL or AFC ≥5) and regular menstrual cycles (21–35 days).Willingness to participate as evidenced by signed informed consent document.

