### Exclusion criteria

Patients with active genital tract infections or systemic infections requiring treatment.Patients with significant congenital or acquired reproductive organ malformations or severe organic lesions.Patients with endocrine disorders that may affect implantation, including: (a) untreated or poorly controlled thyroid dysfunction (defined as TSH < 0.3 mIU/L or > 4.5 mIU/L); (b) hyperprolactinemia (serum prolactin > 25 ng/mL); (c) polycystic ovary syndrome (PCOS) diagnosed according to Rotterdam criteria; (d) luteal phase defect (serum progesterone < 10 ng/mL on cycle day 21).Patients with immunological or hematological disorders that may affect implantation, including: (a) autoimmune diseases; (b) inherited or acquired thrombophilia.Patients exhibiting inadequate endometrial development (thickness <6 mm or Type C pattern) on trigger day.Patients with a history of TORCH infection.Patients with a Body Mass Index (BMI) <18.5 kg/m².

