### Procedure

All participants will receive standard Western medical treatment during their IVF-ET cycles, including ovulation induction medications in the preparatory phase and luteal phase support following embryo transfer. The administration of these foundational medications cannot be fully standardized due to interpatient variability in physiological parameters. Treatment protocols are therefore individualized based on patient characteristics to maximize pregnancy success rates. To address potential confounding, the following IVF cycle characteristics will be prospectively documented for each participant: specific controlled ovarian stimulation protocol (e.g., GnRH agonist long protocol, GnRH antagonist protocol, or others), type and dosage of gonadotropins, embryo stage at transfer (cleavage stage or blastocyst), embryo quality grade, and number of embryos transferred. Acupuncture or sham acupuncture intervention will be administered twice weekly from day 5 of the menstrual cycle until the day before embryo transfer, with a minimum requirement of three completed acupuncture sessions.

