### Sample size

Based on previously reported data, the embryo implantation rate in RIF patients receiving acupuncture combined with hormone replacement therapy (HRT) is estimated at 35.42%, compared with 20.13% in patients receiving HRT alone (21). To detect this difference with a two-sided significance level of α = 0.05 and a power of 90% (1-β = 0.90) using a 1:1 allocation ratio, a total of 358 participants (179 per group) would be required for a fully powered confirmatory randomized controlled trial (calculated using the formula for comparing two independent proportions with continuity correction).

As an exploratory clinical study designed with pragmatic considerations, we determined the sample size through comprehensive evaluation of feasibility constraints rather than formal power calculations. This pragmatic approach is consistent with the methodological guidance for pilot trials, which emphasizes that sample sizes should be based on practical considerations. The final sample of 100 participants (50 per group) has been established after accounting for anticipated recruitment challenges, 24-month study duration limitations, available research funding, and current staffing capacity. We acknowledge that with a sample size of 100, the trial may have limited statistical power to detect small-to-moderate treatment effects. Therefore, the trial is not designed or powered to produce definitive efficacy conclusions, and the results will be interpreted with appropriate caution. The findings will primarily serve to generate preliminary estimates of between-group differences in embryo implantation rate, inform formal power calculations for a subsequent large-scale, multicenter RCT, and evaluate protocol feasibility parameters including recruitment rate, retention rate, and protocol adherence.

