### Statistical analysis

Baseline characteristics will be summarized using descriptive statistics, with continuous variables reported as mean ± standard deviation or median (interquartile range) depending on data distribution, and categorical variables reported as frequencies and percentages. The following baseline characteristics will be collected and compared between groups: age, BMI, duration of infertility, number of previous failed IVF-ET cycles, basal FSH level, AMH level, AFC, endometrial thickness, and number of embryos transferred. Between-group comparisons of baseline characteristics will employ independent samples t-tests or Mann-Whitney U tests for continuous variables, and χ² tests or Fisher’s exact tests for categorical variables, as appropriate.

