Before conducting comparative analysis tests on all variables, a data normality test will be performed first to ensure the appropriateness of the selected comparative analysis methods. For the primary outcome, embryo implantation rate, the unit of analysis is defined as the individual embryo. However, because each participant may contribute multiple embryos, the data exhibit a clustered structure that violates the independence assumption of conventional statistical tests. Therefore, between-group comparisons for the primary outcome will be performed using a Generalized Estimating Equation (GEE) model with a logit link function and a binomial distribution family. An exchangeable correlation structure will be specified to account for within-patient clustering. The model will include treatment group (acupuncture vs. sham acupuncture) as the primary independent variable, and will be adjusted for the following pre-specified clinically relevant covariates: age, BMI, number of previous failed IVF-ET cycles, controlled ovarian stimulation protocol type (categorical), embryo stage (cleavage vs. blastocyst), embryo quality (good vs. fair, dichotomized for analysis), and number of embryos transferred. Results will be reported as odds ratios with 95% confidence intervals and P-values based on robust standard errors. For secondary outcomes, between-group comparisons will employ: 1) χ² or Fisher’s exact tests for dichotomous outcomes (clinical pregnancy rate); 2) independent samples t-tests or Mann-Whitney U tests for continuous variables (reproductive hormone levels). The intention-to-treat population will serve as the primary analysis set, with missing outcome data will be handled using multiple imputation by chained equations (MICE) under the assumption of missing at random (MAR), with sensitivity analyses performed under missing not at random (MNAR) assumptions to assess the robustness of the findings.

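### Transfer type (fresh, frozen or mixed) is left unclear, and the primary GEE model adjusts for number of embryos transferred, and possibly embryo stage and quality, which may be settled only after treatment starts

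*Protocol article*

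**What the plan says.** No section of the protocol article names the study transfer as fresh or frozen. The relevant statements are these.

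- Inclusion criteria: each woman must have "availability of ≥1 good-quality cryopreserved embryo".
- Exclusion criteria: one criterion is "inadequate endometrial development (thickness <6 mm or Type C pattern) on trigger day".
- Procedure: all participants receive standard treatment, "including ovulation induction medications in the preparatory phase and luteal phase support following embryo transfer". To deal with confounding, "the following IVF cycle characteristics will be prospectively documented for each participant: specific controlled ovarian stimulation protocol", and then "type and dosage of gonadotropins, embryo stage at transfer (cleavage stage or blastocyst), embryo quality grade, and number of embryos transferred".
- Procedure, on timing: acupuncture or sham runs twice weekly from cycle day 5 up to the eve of transfer.
- Sample size: the planning rates are taken from a cited study of "acupuncture combined with hormone replacement therapy (HRT") against HRT alone.
- Statistical analysis, baseline paragraph: the characteristics to be compared and tested between groups include "basal FSH level, AMH level, AFC, endometrial thickness, and number of embryos transferred".
- Statistical analysis, primary outcome: the GEE model contains treatment group and seven covariates. Three are age, BMI and the number of earlier failed cycles. The list continues with "controlled ovarian stimulation protocol type (categorical), embryo stage (cleavage vs. blastocyst" and ends with embryo quality and number transferred. No unadjusted or less adjusted analysis of the primary outcome is described.

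**The concern.** A covariate in the primary model of a randomised trial should be fixed before allocation. If it is settled later and treatment can influence it, the coefficient for treatment no longer carries the whole effect: what passes through the covariate is adjusted away. Whether that applies here depends on the type of transfer, which the article leaves open, except for number transferred, where it applies whatever the type.

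The stake is the pilot's main product. The Abstract and the Sample size section say that the trial exists to supply effect estimates for planning a larger trial. The primary odds ratio comes only from this adjusted model. If the model conditions on consequences of treatment, the next trial would be sized on an estimate that is not the total effect. A reader also could not tell which kind of cycle the estimate describes.

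**Working it through.** The article gives no figure of its own on which this point turns, so the check is mainly a comparison of sections. The planning rates are used only for scale.

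**Step 1. Which transfer type do the sections imply?**

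- Towards frozen: the cryopreserved embryo required at entry. The HRT planning rates lean the same way, but weakly, because they describe the cited study's patients.
- Towards a stimulated cycle: ovulation induction for all participants, stimulation protocol and gonadotropin dosage recorded prospectively, and a trigger-day criterion.
- Neutral: the Discussion's assumption of ovulation around day 14 and about 13 days of treatment.

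Nothing reconciles these statements or says that both types are admitted.

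**Step 2. When is each covariate settled?** The article does not date randomisation within the cycle, but allocation must precede the first session. Anything settled after the day 5 session is therefore post-randomisation.

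| Covariate | Fresh stimulated cycle | Frozen transfer |
|---|---|---|
| Age, BMI, earlier failed cycles | before | before |
| Stimulation protocol | part of the treated cycle; usable if chosen before randomisation | describes an earlier retrieval cycle |
| Embryo stage | after treatment starts | largely before, apart from which embryo is chosen |
| Embryo quality | after treatment starts | largely before, apart from which embryo is chosen |
| Number transferred | after treatment starts | after treatment starts |

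One of the seven covariates (number transferred) follows the start of treatment in both columns. Three of the seven do so if the transfer is fresh.

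**Step 3. How much effect could be adjusted away?** The documents do not say, so this is an illustration only. Assume a fresh cycle in which acupuncture raises the share of good-quality embryos from 65% to 75%, and in which good and fair embryos implant at 28% and 18%. The part of the risk difference passing through quality is

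(0.75 − 0.65) × (0.28 − 0.18) = 0.010, or 1.0 percentage point.

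The planning difference is 35.42 − 20.13 = 15.29 points, so this is 1.0 / 15.29 = 6.5% of it. With half the assumed shift in quality the figure is 0.5 point, and with no shift it is 0. Nothing comparable can be worked out for stage or number transferred.

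**Step 4. What does the covariate list cost in model terms?** Assume three stimulation categories, after the examples in the Procedure section (2 terms). The non-intercept terms are then treatment, age, BMI, earlier failures, stimulation (2), stage, quality and number: 9 in all. The mean planning rate is (35.42 + 20.13) / 2 = 27.775%. Assume that all 100 women reach transfer, with 1, 1.5 or 2 embryos each:

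| Embryos per woman | Implantations | Per term, 9 terms | Per term, 6 terms | Per term, 4 terms |
|---|---|---|---|---|
| 1 | 27.8 | 3.1 | 4.6 | 6.9 |
| 1.5 | 41.7 | 4.6 | 6.9 | 10.4 |
| 2 | 55.6 | 6.2 | 9.3 | 13.9 |

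Four terms are treatment, age, BMI and earlier failures; six add stimulation protocol.

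**The case against.** The case for the sponsor has several parts.

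- The conflict is by implication. Having a frozen embryo available does not say that it is the one transferred, and a trigger day or ovulation induction can also occur in a frozen cycle without HRT. A mixed population is a third reading. This stands: a reader might infer a flat contradiction between two named cycle types, but neither type is named. What remains is that the sections pull apart and nothing reconciles them.
- A reader might infer that the covariates are wrong whichever type applies. The documents do not support that. If fresh, stimulation protocol is a legitimate covariate provided that it is fixed before randomisation. If frozen, embryo stage and quality are largely set beforehand, and a stimulation term from an earlier cycle mainly costs precision.
- A reader might also infer that omitting endometrial preparation, or fresh versus frozen status, biases the comparison. It does not, because randomisation protects it; only precision is at stake. An item missing from a condensed article may also be on the case report form.
- The Discussion places the mechanism in endometrial receptivity and blood flow, so an effect conditional on embryo characteristics could be close to what is wanted. This has some force, but the plan does not state that target. The Introduction also hypothesises action through the hypothalamic-pituitary-ovarian axis, so an influence on embryos in a stimulated cycle cannot be set aside.
- The trial is expressly not definitive. That limits the harm, but estimating an effect for the next trial is the stated purpose.

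**Conclusion.** The point holds in a limited form. The transfer type is unclear across the Inclusion criteria, Exclusion criteria and Procedure sections. The primary model adjusts for number transferred, which is settled after treatment begins under any reading and is mislabelled as baseline. It also adjusts for embryo stage and quality, which are post-treatment in any fresh stimulated cycle. The primary odds ratio may therefore not estimate the total effect.

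The amount is unknown. The 1.0-point illustration rests wholly on assumed inputs, is on the risk-difference scale and shows direction only. The counts of implantations per term rest on assumed embryo numbers and an assumed three-level stimulation factor.

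A reader might take the endometrial thickness in the baseline list to be the trigger-day measurement. The baseline paragraph gives no timing for it, so no fault is claimed there.

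**What to change.** 1. Reconcile the Inclusion criteria, Exclusion criteria, Procedure and Statistical analysis sections on whether transfers are fresh, frozen or mixed. Which applies is for the investigators to state.
2. Restrict the primary GEE model to covariates fixed before randomisation: age, BMI and number of earlier failed cycles. Add stimulation protocol or cycle type only where it applies to the transfer and is fixed before randomisation.
3. Move number transferred to a secondary adjusted model, together with embryo stage and quality wherever they are not fixed before randomisation.
4. Report number transferred by arm as a post-randomisation characteristic, and remove it from the baseline tests.

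The cost is rewording, one extra secondary analysis and some loss of precision from leaving prognostic embryo variables out of the primary model. The shorter model offsets part of this by estimating fewer terms. The odds ratios from the two models should not be subtracted to obtain a mediated effect, because an odds ratio changes with the covariates in the model even when none of them is a mediator.

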### Outcomes

#### Primary outcomes

The primary outcome is embryo implantation rate, defined as the number of implanted embryos per transferred embryo (18).

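### The pilot is meant to estimate a difference in implantation rate for later sample sizing, but the only primary effect measure given an interval is a covariate-adjusted odds ratio

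*Protocol article*

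**What the plan says.** All references are to the protocol article.

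- **Primary outcomes:** the endpoint is a rate. "The primary outcome is embryo implantation rate, defined as the number of implanted embryos per transferred embryo".
- **Sample size:** the findings will primarily "generate preliminary estimates of between-group differences in embryo implantation rate, inform formal power calculations" for a later multicentre trial, and will also evaluate feasibility. The calculation shown for that later trial rests on two absolute rates, 35.42% with acupuncture plus hormone replacement therapy "compared with 20.13% in patients receiving HRT alone", with a "two-sided significance level of α = 0.05" and "a power of 90% (1-β = 0.90) using a 1:1 allocation ratio". It arrives at 179 per group.
- **Statistical analysis:** the primary comparison is a GEE with logit link, binomial family and exchangeable correlation within women. It is adjusted for age, BMI, previous failed cycles, stimulation protocol, embryo stage, embryo quality and number of embryos transferred. "Results will be reported as odds ratios with 95% confidence intervals and P-values based on robust standard errors". No rate difference, arm rate with an interval, or standardisation step is named for this outcome.
- **Abstract and Discussion:** the aim is put more loosely, as estimating effect sizes (no scale given) and assessing feasibility.

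**The concern.** The plan chooses a measure that does not fit the use it declares. The next trial is to be sized with a two-proportion formula, which needs two rates. Two problems follow.

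First, an odds ratio by itself fixes neither a difference nor a sample size. Both depend on the control rate.

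Second, the GEE averages over women, but its treatment odds ratio is still conditional on the seven covariates. Odds ratios are non-collapsible: with prognostic covariates, the adjusted odds ratio lies further from 1 than the odds ratio formed from the two arm rates, even with perfect balance and no bias. Applying it to the crude control rate gives too large a difference and so too small a trial. A larger pilot would not remove this error.

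The crude arm rates do not fully close the gap. The article itself recognises that embryos from the same woman are not independent, so a simple binomial interval on embryo counts would not be valid. A pilot meant for sizing needs the difference together with an uncertainty that allows for clustering.

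**Working it through.** **Inputs from the Sample size section:** p1 = 0.3542, p2 = 0.2013, two-sided alpha 0.05 (z = 1.960), power 90% (z = 1.2816), 1:1 allocation. **Assumed, not in the document:** the covariates produce a normally distributed linear predictor with SD s on the logit scale, with s from 0.25 to 1.25.

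**1. The plan's own figure.** With pooled variance under the null, mean rate p = 0.27775 and no continuity correction:

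n = [1.960 × √(2p(1−p)) + 1.2816 × √(p1(1−p1) + p2(1−p2))]² / (p1−p2)²
= [1.960 × 0.6334 + 1.2816 × 0.6241]² / 0.1529² = 178.2, so 179 per group and 358 in total.

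This matches the article. The article says a continuity correction was used; with it the result is 192 per group. That is a separate matter. The uncorrected formula is used below so that results compare with 179.

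**2. The planning rates on each scale.**
- Difference: 0.3542 − 0.2013 = 0.1529, or 15.3 points.
- Rate ratio: 0.3542 / 0.2013 = 1.76.
- Marginal odds ratio: (0.3542/0.6458) / (0.2013/0.7987) = 0.5485 / 0.2520 = 2.18.

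**3. An odds ratio does not fix the difference.** Hold the odds ratio at 2.18 and vary the control rate over an assumed range:

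| Control rate | Difference (points) | n per group |
|---|---|---|
| 10% | 9.5 | 293 |
| 15% | 12.7 | 216 |
| 20.13% | 15.3 | 179 |
| 30% | 18.3 | 149 |
| 40% | 19.2 | 141 |

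**4. Effect of conditioning on covariates.** For each s, solve for arm intercepts a0 and a1 so that the logistic function of (a + s·Z), averaged over standard normal Z by Gauss-Hermite quadrature, equals 0.2013 and 0.3542. The conditional odds ratio is exp(a1 − a0). The naive step multiplies the crude control odds, 0.2520, by it and converts back to a rate. At s = 1.0: 0.2520 × 2.499 = 0.630; 0.630/1.630 = 0.3865; 0.3865 − 0.2013 = 18.5 points. The true power in the last column is for the resulting n when the real rates are 0.2013 and 0.3542.

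| Assumed s | Conditional odds ratio | Naive difference (points) | n per group | True power |
|---|---|---|---|---|
| none | 2.18 | 15.3 | 179 | 90% |
| 0.25 | 2.20 | 15.5 | 174 | 89% |
| 0.5 | 2.26 | 16.1 | 162 | 87% |
| 0.75 | 2.36 | 17.2 | 144 | 83% |
| 1.0 | 2.50 | 18.5 | 126 | 78% |
| 1.25 | 2.67 | 20.1 | 108 | 71% |

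**5. Set against sampling error.** From s = 0.5 to 1.25 the shift in the log odds ratio is 0.04 to 0.21. With 50 or 100 embryos per arm, treated as independent, its standard error √[1/(n·p1(1−p1)) + 1/(n·p2(1−p2))] is 0.46 or 0.33. In this pilot the shift is smaller than the noise, but unlike the noise it has a fixed direction and does not shrink with sample size.

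**The case against.** The strongest reply has five parts.

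- **The rates will exist anyway.** The endpoint is a rate, so counting it by arm gives both rates and their crude difference, and nothing in the article excludes reporting them. This stands. A reader might infer that the pilot cannot deliver the quantity it was set up to estimate; the document does not support that. What is missing is a specified difference with a valid interval.
- **The wording is loose.** The Abstract and Discussion speak of effect sizes, and an odds ratio is one. Feasibility is a co-aim, and the Discussion calls it a primary objective. This stands in part. The Sample size section is more specific, though: it names differences in rate directly after a calculation built on two rates.
- **The sizing error needs a misuse that nobody proposes.** This stands. The article nowhere says the adjusted odds ratio will be applied to a control rate, and a successor planned as in the Sample size section would use two arm rates. The losses of power in the working are therefore conditional.
- **The covariate SD is assumed.** This stands. Eligibility is narrow (age 25–40, normal ovarian reserve, several disorders excluded), which may reduce prognostic spread, and at SD 0.25 the effect is negligible.
- **This is detail for the SAP.** Supplementary measures often are, and an article need not list them. Here, however, the article does not leave the measure open: it fixes one, and that one does not match the purpose it states. Making the odds ratio secondary would be a matter of preference and is not asked for.

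**Conclusion.** The point holds as a mismatch between stated purpose and specified reporting. The purpose is a difference in implantation rate for use in a two-rate power calculation; the only primary effect measure given a confidence interval is a covariate-adjusted odds ratio. That mismatch rests on the text alone.

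The size of any harm is conditional. If the adjusted odds ratio were applied to the crude control rate, the 15.3-point difference would be read as 15.5 to 20.1 points, and the later trial's power would be about 89% to 71% instead of 90%. This rests on the article's planning rates, an assumed normal covariate SD of 0.25 to 1.25 on the logit scale, and the same independent-observation formula the article uses. The lower end is trivial, and the upper end needs strongly prognostic covariates.

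The planned GEE is not invalid, and the odds ratio is a legitimate measure to report. The change is worth making because it is inexpensive and serves the use that the pilot declares.

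**What to change.** In the Statistical analysis section, keep the odds ratio and add the standardised implantation rate in each arm and their difference (acupuncture minus sham) with a 95% CI, from the GEE already planned. Predict every transferred embryo's probability under each assignment, average under each, and subtract. Take the interval from the delta method on the robust covariance, or from a bootstrap that resamples women, and combine it across the multiply imputed datasets. In the Sample size section, state that these rates, not the adjusted odds ratio, will inform the later power calculation.

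This needs no new data, participants or visits. It does need a modest script beyond standard SPSS output, including the pooling over imputations. The model will also be thin: at the planning rates, 50 to 100 embryos per arm give about 28 to 56 implantations in all (50 × 0.5555 = 27.8; 100 × 0.5555 = 55.6). The script should therefore be tested before the database is locked.

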### Randomization and blinding

A total of 100 eligible participants will be randomly allocated to either the experimental or control group in a 1:1 ratio using permuted block randomization. The allocation sequence will be concealed through sequentially numbered, opaque, sealed envelopes to ensure randomization integrity. This trial employs a single-blind design wherein participants will remain blinded to their group assignment throughout the trial. Practitioners administering acupuncture will necessarily be unblinded due to the inherent characteristics of the intervention. To minimize detection bias, outcome assessors (including ultrasound technicians evaluating gestational sacs and laboratory personnel analyzing hormone levels) will be strictly segregated from the acupuncture procedures and will remain blinded to group allocation. Furthermore, the statistician responsible for data analysis will also be blinded until the analysis plan is finalized and the database is locked. While performance bias cannot be entirely eliminated due to practitioner unblinding, the use of a standardized sham protocol aims to mitigate differential participant-provider interactions.

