#### Secondary outcomes

1. Clinical pregnancy rate. Presence of a gestational sac with embryonic cardiac activity confirmed by transvaginal ultrasound at 30 days post-embryo transfer (19).

2. Hormonal profiles. Serum levels of β-human chorionic gonadotropin (β-hCG), luteinizing hormone (LH), progesterone (P), and estradiol (E2) measured at 14 days post-transfer.

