The primary outcome of this study is embryo implantation rate, as our primary focus is determining whether IVF-ET successfully achieves embryo implantation. This selection is based on the mechanistic focus and practical constraints of this pilot trial. First, the study examines whether brief acupuncture during the peri−implantation window may directly influence embryo attachment through potential enhancement of endometrial receptivity and local blood flow. Second, limited follow−up time and funding make it infeasible to track participants to live birth, which requires around 9 months of monitoring after transfer. Third, although clinical pregnancy and live birth rates are more clinically meaningful, they are affected by many post−implantation factors unrelated to acupuncture’s mechanism. In a small sample, these factors would dilute the intervention effect and reduce the reliability of estimated effect sizes. Thus, implantation rate is a direct and biologically appropriate surrogate that optimizes the signal−to−noise ratio in this exploratory study. For secondary outcomes, we have chosen clinical pregnancy rate and reproductive hormone levels. As quantifiable objective measures, reproductive hormones serve as important biomarkers influencing pregnancy outcomes and can help elucidate the potential mechanisms through which the intervention may exert its effects. Nevertheless, we acknowledge that embryo implantation rate is a surrogate endpoint rather than a definitive clinical outcome. Consequently, the findings of this pilot trial are not intended to directly guide clinical decision−making, but rather to inform the design and power calculations of future confirmatory trials with more clinically meaningful endpoints such as live birth rate.

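### Clinical pregnancy is compared without covariates; the test is valid, but a logistic model with two covariates would be a cheap, minor improvement

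*Protocol article*

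**What the plan says.** All references are to the protocol article.

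- **Test for clinical pregnancy.** The Statistical analysis section assigns "χ² or Fisher’s exact tests for dichotomous outcomes (clinical pregnancy rate") and names no covariate for it. The sensitivity analyses described there concern the primary outcome only.
- **Primary outcome.** The same section fits a GEE model to embryo implantation that "will be adjusted for the following pre-specified clinically relevant covariates: age, BMI, number of previous failed IVF-ET cycles", plus stimulation protocol, embryo stage, embryo quality and number transferred.
- **Data available.** The baseline list in that section is "age, BMI, duration of infertility, number of previous failed IVF-ET cycles, basal FSH level, AMH level, AFC, endometrial thickness, and number of embryos transferred".
- **Endpoint.** The Secondary outcomes section defines clinical pregnancy as "Presence of a gestational sac with embryonic cardiac activity confirmed by transvaginal ultrasound at 30 days post-embryo transfer", which is one yes/no result per woman.
- **Allocation.** The Randomization and blinding section allocates "in a 1:1 ratio using permuted block randomization" and mentions no stratification factor.
- **Size and rates.** The Sample size section gives 100 women (50 per arm) and implantation rates of 35.42% and 20.13%. The article gives no clinical pregnancy rate and no measure of how strongly any covariate predicts outcome.

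**The concern.** Two variables that the authors regard as relevant to implantation play no part in the comparison of clinical pregnancy, although both outcomes come from the same women after the same transfers. Baseline balance will be tested, but nothing found there feeds into the clinical pregnancy result.

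What is at stake is the quality of one estimate. If the arms happen to differ on age or failed-cycle count, the crude difference in pregnancy rates absorbs part of that difference. A pilot whose aim is to estimate effects has some interest in avoiding this, and the Discussion calls the outcome one of the "although clinical pregnancy and live birth rates are more clinically meaningful" endpoints. Adjustment for prognostic covariates may also narrow the interval, but by how much depends on figures that the article does not contain.

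**Working it through.** **Inputs.** From the article: 50 per arm; p1 = 0.3542 and p2 = 0.2013 (implantation rates, used here as a stand-in for pregnancy rates); two-sided α = 0.05; age 25 to 40. Assumed: the correlation rho between covariate and outcome, or equivalently the AUC of the two covariates together.

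**1. The plan's own figure.** There is none for clinical pregnancy. The implantation calculation gives 179 per group by the pooled two-proportion formula at 90% power without continuity correction, and 192 with it. The article says that the correction was used. That mismatch is a separate matter and does not affect this point.

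**2. Precision of the crude comparison at 50 per arm.**
SE = √[(0.3542×0.6458 + 0.2013×0.7987)/50] = 0.0883.
z = 0.1529/0.0883 = 1.73, so power is about 41% (39.9% with the pooled-variance formula).
Expected pregnancies = 50×(0.3542 + 0.2013) ≈ 28.

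**3. Chance imbalance.**
The SD of a standardised mean difference between arms is √(2/50) = 0.20.
P(|difference| > 0.3 SD) = P(|Z| > 1.5) ≈ 13%.
For scale: if age is uniform on 25 to 40, its SD is 15/√12 = 4.33 years, so 0.3 SD is about 1.3 years.
Within that tail the mean imbalance is about 0.39 SD. The outcome SD is √(0.278×0.722) ≈ 0.45. The expected shift in the crude risk difference is rho × 0.45 × 0.39:
- rho 0.2: about 3.5 points
- rho 0.3: about 5.2 points

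Simulation with 200,000 trials per setting gives 3.2 points at rho of about 0.19 and 4.8 at about 0.28. In a smaller simulation (4,000 trials per setting), the standardised estimate from an adjusted logistic model was off by at most 0.8 points in the same tail.

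**4. Precision and power after adjustment.** Simulated trials of 100 women (4,000 per setting), with age uniform on 25 to 40 and failed cycles as 2 + Poisson(0.8), both assumed:

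| AUC of the two covariates | Variance ratio, adjusted/crude | Power, χ² | Power, adjusted Wald | Power, adjusted likelihood ratio |
|---|---|---|---|---|
| 0.50 | 1.03 | 40.6% | 39.2% | 41.1% |
| 0.58 | 1.005 | 39.7% | 39.5% | 41.2% |
| 0.66 | 0.96 | 40.6% | 41.0% | 43.1% |
| 0.73 | 0.88 | 39.8% | 44.1% | 46.4% |

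Fisher's exact test has 31% to 33% power throughout. The large-sample approximation, variance × (1 − rho²), points the same way: from 41.0% unadjusted to 42.4% at rho 0.2 and 44.3% at rho 0.3.

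**5. Type I error** (3,000 null trials per setting): χ² 4.8% to 5.3%, Fisher 2.4% to 3.1%, adjusted Wald 4.6% to 5.1%, adjusted likelihood ratio 5.2% to 5.9%. Part of the likelihood-ratio test's power advantage therefore comes from a slightly liberal test.

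**The case against.** The strongest reply is that nothing here is wrong. Under randomisation an unadjusted test already allows for chance imbalance in its error rate, and step 5 confirms it. Averaged over all randomisations the crude estimate has no bias; the 3 to 5 points apply only within the 13% of trials selected for imbalance, and they are roughly half the 8.8-point standard error or less. This stands, and it is why the point is minor.

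It is also fair to say that the outcome is secondary in a pilot. The Sample size section puts the estimate of implantation first, and the Discussion explains that clinical pregnancy was not made primary because later factors unrelated to the proposed mechanism affect it. Eligibility (age 25 to 40, at least two failed cycles, normal ovarian reserve) may also narrow the spread of the covariates and weaken their prediction.

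A reader might infer three stronger claims that the document does not support:

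- **That precision is being given away at no cost.** With weak covariates, adjustment slightly loses power, and no passage says how strong they are.
- **That clinical pregnancy will be reported without an effect size or interval.** The article names the test but does not exclude these. A two-by-two table yields them directly, and reporting detail may sit in a fuller document.
- **That adjustment would put this result on the same footing as the primary analysis.** The two differ in unit (woman against embryo) and in event, and two covariates are not the primary model's seven.

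What the reply does not remove is that the article fixes an unadjusted method although two suitable covariates are at hand.

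**Conclusion.** The point holds as a minor improvement, not as the correction of an error. The planned χ² or Fisher test is valid. Its estimate is left exposed to chance imbalance on two covariates that the authors themselves consider relevant: about a 13% chance of an imbalance above 0.3 SD on any one covariate, with a resulting shift of about 3 to 5 percentage points at rho 0.2 to 0.3, against under 1 point after adjustment. The precision effect runs from a variance increase of about 3% to a reduction of about 12%, or about −1 to +4 points of Wald power.

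These sizes rest on implantation rates standing in for pregnancy rates, on assumed covariate distributions, and on an assumed range of prognostic strength. With barely prognostic covariates the benefit vanishes.

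**What to change.** In the Statistical analysis section, replace the first item under secondary outcomes with a per-woman logistic regression of clinical pregnancy on treatment group, age (continuous) and count of earlier failed cycles. Report the standardised (marginal) risk difference and the odds ratio, each with a 95% CI. Keep the χ² or Fisher test as the unadjusted sensitivity analysis.

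Stop at these two covariates. With about 28 expected pregnancies, treatment plus two covariates leaves about 28/3 ≈ 9 events per slope. Carrying over all seven covariates of the primary model would leave at most 28/8 = 3.5.

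The cost is one sentence in the plan and a few lines of code, with no new data. The downside is two extra slopes on a small number of events, and a loss of about 1 point of power if the covariates prove barely prognostic.
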